**Methods:**

The primary aim of the randomized, controlled *Optimization of Polypharmacy in Geriatric Oncology (OPTIMAL)* trial is to test whether an advisory letter with the results of a comprehensive medication review conducted with the Fit fOR The Aged (FORTA) list to the caring physician in rehabilitation clinics improves the quality of life (QoL) of older cancer patients exposed to polypharmacy more than usual care. The FORTA list detects medication overuse, underuse, and potentially inappropriate drug use among older adults. In the oncology departments of approximately 10 German rehabilitation clinics, we aim to recruit 514 cancer patients (22 common cancers; diagnosis or recurrence requiring treatment in the last 5 years; all stages) who are ≥ 65 years old, regularly take ≥ 5 drugs, and have ≥ 1 medication-related problem. All necessary information about the patients will be provided to a pharmacist at the coordinating center (German Cancer Research Center, Heidelberg), who will perform randomization (1:1) and conduct the medication review with the FORTA list. For the intervention group only, the results are sent by letter to the treating physician in the rehabilitation clinics, who shall discuss medication changes with the patient at the discharge visit, as well as implement them afterwards and disclose them in the discharge letter to the general practitioner. The control group gets the usual care provided in German rehabilitation clinics, which usually does not include a comprehensive medication review but can include medication changes. Patients will be blinded, as they cannot know whether proposed medication changes were part of the study or part of usual care. Study physicians cannot be blinded. The primary endpoint will be the EORTC-QLQ-C30 global health status/QoL score, assessed via self-administered questionnaires 8 months after baseline.

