No written informed consent to participate.No sufficient mental and physical capabilities to fill self-administered questionnaires.No sufficient knowledge of the German language.Missing information needed to conduct the medication review with the FORTA list (medical diagnoses and drugs used at the start of rehabilitation).No medication related problem at baseline (FORTA score = 0).Missing baseline information needed for the primary endpoint (change in EORTC-QLQ-C30 GHS/QoL scale).

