Appropriate use: The medication is indicated; a drug classified as A (indispensable) or B (beneficial) is prescribed.PIM use: The medication is indicated but a drug classified as C (questionable) or D (avoid) in the FORTA list is given despite available classes A (indispensable) or B (beneficial) alternatives.Underuse: An indication is not treated.

2nd step: Drugs not rated in the first step will then be checked and rated as follows:

Overuse: The medication is prescribed in the absence of an appropriate indication.Appropriate use: The medication is appropriately prescribed according to clinical guidelines for a disease not listed in the FORTA list, which is limited to 30 diseases.

The pharmacist will subsequently calculate the FORTA sub-scores for underuse, overuse, and PIM use for every patient and sum the three scores up to obtain the total FORTA score. Each medication underuse and overuse scores 1 point. Each PIM use scores 2 points.

For patients randomized to the intervention group, the pharmacist will fax an advisory letter to the study physicians stating suggested medication changes to overcome PIM use (by replacing drugs with a C or D rating by drugs with an A or B rating), underuse (by adding drugs with an A or B rating), and overuse (by withdrawal of drugs without indications). If the FORTA list suggests no medication changes, the letter will contain only the sentence: “No medication changes suggested”. For patients randomized to the control group, the letter will include the same sentence: “No medication changes suggested”.

Thus, the study physicians will be partly blinded because they cannot know the randomization group for patients for whom they received the sentence “No medication changes suggested” in the advisory letter from the coordinating center. However, they could still correctly guess that patients with medication changes suggested in the letter are in the intervention group. Thus, due to the nature of the intervention, the study physicians cannot be fully blinded and the study design is only a single-blinded study (only study participants will be blinded).

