#### 2nd study visit for potential medication changes (week 3 of rehabilitation)

The study physician will have a visit with the study participants to discuss his/her medication. This should take place for both the intervention and control group to avoid accidental unblinding of study participants. For study participants in the intervention group, the study physician can follow the advice from the letter of the pharmacist, who conducted the comprehensive medication review with the FORTA list. However, the study physician is free to decide which medication changes he or she will suggest to his/her patient and the patient is also free to decide which changes he/she wants to be implemented.

To maintain blinding of study participants, it is prohibited for the study physician to tell the study participant about the advisory letter he received from the coordinating center or to show the letter to the study participant. Furthermore, it is important for the blinding of study participants that the study physician in addition provides the patient the information that these medication changes could either mean that he/she is part of the intervention group of the study or that these medication changes were based on the physician’s own judgement because the study physicians are allowed to suggest medication changes as part of usual care also to patients randomized to the control group.

In the control group receiving usual care, medication reviews and changes are not prohibited as they are sometimes done as part of usual care in the German oncologic rehabilitation setting. However, medication reviews are usually not comprehensive by checking the total medication with a medication management software and/or PIM lists. To ensure that intervention and control group are treated differently enough to test the intervention, we will not collaborate with study physicians who conduct comprehensive medication reviews with medication management software or apply a PIM list as part of usual care for older cancer patients.

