If no medication changes are discussed in the 2nd study visit, the study physician shall give the study participant the information that this could either mean that the medication review result was that no medication changes are necessary or that they were in the control group. As the exact wording is important in the communication with the patient to avoid accidental unblinding, the coordinating center will provide cards with the text to be communicated from the study physician to the patient in the two different scenarios (Medication changes suggested or not). The study physician shall read the text of the respective card to the patient.

Medication changes to be implemented after the 2nd visit should be documented by the study physician in a standardized form and communicated to the study participants’ general practitioners in the discharge letter. The standardized form should be mailed to the coordinating center.

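### With FORTA score 0 excluded, the no-change letter should go almost only to controls, so the partial-blinding claim is unsupported and the letter does not reflect any eligible control's review

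*Protocol article*

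**What the plan says.** - **Eligibility.** The exclusion criteria under Study population list "No medication related problem at baseline (FORTA score = 0". The abstract likewise requires that patients "regularly take ≥ 5 drugs, and have ≥ 1 medication-related problem".
- **Scoring.** In the section on randomization, blinding and medication review, "Each medication underuse and overuse scores 1 point", and each PIM use scores 2. A PIM is counted only where an A- or B-rated alternative is available.
- **Letters.** In the intervention arm the letter proposes replacing PIMs, adding drugs for underuse and withdrawing drugs for overuse. If FORTA suggests nothing, it contains a single sentence saying so. "For patients randomized to the control group, the letter will include the same sentence".
- **Blinding claim.** The section concludes that physicians are partly blinded, because "they cannot know the randomization group for patients for whom they received the sentence". It concedes that letters with suggestions point to the intervention arm and calls the trial single-blinded. The abstract says without qualification that physicians cannot be blinded.
- **Control condition.** "In the control group receiving usual care, medication reviews and changes are not prohibited" (2nd study visit).
- **Patient card.** If no changes are discussed, the patient is told that "this could either mean that the medication review result was that no medication changes are necessary or that they were in the control group".

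**The concern.** The partial-blinding argument needs a real pool of intervention patients whose letter carries no suggestion, so that such a letter leaves the physician uncertain. The entry criterion appears to empty that pool. If so, the letter shows allocation in both arms to anyone who knows the criteria, and site staff do: they screen with a checklist that states them.

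The second issue is what the comparator receives. Every correctly enrolled control has at least one FORTA problem, yet the centre that performs the review writes to the physician that no changes are suggested, shortly before the week 3 medication visit. Usual care contains no such message. A physician who takes it as the outcome of a review could make fewer of the changes that usual care would have included.

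The prescription monitoring would not show this. Each physician's baseline is taken from his or her first 10 controls, whose letters already carry the sentence, and action follows only if improvement among controls increases. The week 3 FORTA scores depend most directly on these decisions; the primary quality-of-life endpoint depends on them indirectly.

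**Working it through.** No figure in the plan depends on physician blinding. For completeness, the sample size reproduces. With difference 5.86, SDs 16.15 and 27.22 and 231 per arm, the standard error is √((16.15² + 27.22²)/231) = √(1001.75/231) = 2.08. The Satterthwaite t-test then has power 0.801, and 462/0.90 rounds up to 514. None of this is at issue.

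**Step 1: can an eligible intervention patient get an empty letter?** Let u, o and p be the numbers of underuse, overuse and PIM items.
- Score = u + o + 2p (scoring rule).
- Suggestions = u + o + p (each item type is tied to add, withdraw or replace).
- Eligible means score ≥ 1, so at least one of u, o, p is ≥ 1, and therefore suggestions ≥ 1.

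With each count running from 0 to 5 there are 6³ − 1 = 215 eligible combinations, and none has zero suggestions. This takes the tie between item and suggestion as given. It confirms the logic of the stated rules and does not test whether the tie always holds in practice.

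**Step 2: what does a no-change letter tell the physician?** Let q be the share of intervention letters without suggestions. All control letters carry the sentence. With 1:1 allocation,

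P(control | no-change letter) = 1/(1 + q).

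The stated rules give q = 0. The document gives no other value, so the remaining rows are assumptions.

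| q | P(control) | empty intervention letters out of 257 |
|---|---|---|
| 0 | 1.00 | 0 |
| 0.01 | 0.99 | 2.6 |
| 0.05 | 0.95 | 12.9 |
| 0.10 | 0.91 | 25.7 |
| 0.20 | 0.83 | 51.4 |

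(257 = 514/2.) The probability falls to one half only if q = 1, that is, if no intervention patient received any advice.

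**Step 3: does the sentence reflect the review for controls?** The same entry criterion applies to both arms, so every eligible control has a score of at least 1. The sentence reflects the review result of none of them.

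**Step 4: the card.** Its first explanation, that the review found no change necessary, is ruled out for eligible patients by Step 1. For controls the second explanation is true. For an intervention patient whose physician takes up none of the advice, which the protocol allows, neither explanation is true.

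**The case against.** Several points on the other side stand.

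- **Certainty is not proven.** A reader might infer that the sentence identifies a control in 100% of cases. Three gaps prevent that. Underuse is scored for any untreated indication, without the requirement of an available A- or B-rated drug that applies to PIMs, so an underuse item might yield no suggestion. Prescription monitoring refers to the FORTA score of the optimal medication, which need not be 0 (although the per-protocol definition under Statistical methods uses a plain cut-off of more than 2, which fits an optimum of 0). And the text has the pharmacist check inclusion and randomize before it describes the review, without saying that the FORTA = 0 check comes first. Such cases are probably few, but they make the claim almost only, not only.
- **Physician blinding is not relied on.** The trial is labelled single-blind, the primary endpoint is self-reported on questionnaires mailed by the coordinating centre, and no analysis or sample-size input uses partial physician blinding.
- **The two harms act on different physicians.** One who infers that the patient is a control will not read the sentence as a clean review; one who reads it so has not been unblinded. They cannot both be charged in full.
- **Drift of the comparator is possible, not shown.** Both arms have a medication visit, changes are allowed in controls, and physicians are told to keep their routine care unchanged.
- **The cards themselves are not shown,** nor whether patients are told of the requirement for at least one problem.

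**Conclusion.** The point holds in limited form. Under the protocol's own eligibility, scoring and letter rules, an intervention letter without suggestions should essentially never occur, so the statement that physicians cannot know the group claims a property the design does not have. The probability that a no-change letter belongs to a control is 1.00 as written, and still 0.91–0.95 if 5–10% of intervention letters were empty, which is an assumption. Separately, the control letter carries a message that usual care does not contain and that reflects no eligible control's review.

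Two stronger readings are not supported. One is that the contrast is inflated by some number of points in favour of the intervention. That would need the share of controls who would otherwise have had changes, the share of those changes the letter stops, and their effect on quality of life; the document gives none of these, so the effect cannot be computed. The other is that participant blinding fails. It is not directly broken, because physicians may change or leave medication in either arm. The single-blind label and the sample size are unaffected.

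**What to change.** Reconcile the exclusion criteria, the section on randomization, blinding and medication review, and the 2nd study visit text, before the first patient is recruited:

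1. State that the FORTA = 0 check is completed before randomization, so that no patient is excluded on this ground afterwards.
2. Delete the partial-blinding claim and say, as the abstract does, that physicians are not blinded.
3. Replace the control-letter sentence with neutral wording that implies no review result, for example that no study advice is issued for this participant.
4. Reword the no-change card so that it is true for eligible patients in both arms, including intervention patients for whom no advice is taken up.

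The cost is a letter template, a card and a few protocol sentences; no sample-size figure or analysis changes. The small downside is that the control letter then shows openly that no study advice is given, which a physician who knows the entry criteria can already infer.

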#### 2nd study visit for potential medication changes (week 3 of rehabilitation)

The study physician will have a visit with the study participants to discuss his/her medication. This should take place for both the intervention and control group to avoid accidental unblinding of study participants. For study participants in the intervention group, the study physician can follow the advice from the letter of the pharmacist, who conducted the comprehensive medication review with the FORTA list. However, the study physician is free to decide which medication changes he or she will suggest to his/her patient and the patient is also free to decide which changes he/she wants to be implemented.

To maintain blinding of study participants, it is prohibited for the study physician to tell the study participant about the advisory letter he received from the coordinating center or to show the letter to the study participant. Furthermore, it is important for the blinding of study participants that the study physician in addition provides the patient the information that these medication changes could either mean that he/she is part of the intervention group of the study or that these medication changes were based on the physician’s own judgement because the study physicians are allowed to suggest medication changes as part of usual care also to patients randomized to the control group.

In the control group receiving usual care, medication reviews and changes are not prohibited as they are sometimes done as part of usual care in the German oncologic rehabilitation setting. However, medication reviews are usually not comprehensive by checking the total medication with a medication management software and/or PIM lists. To ensure that intervention and control group are treated differently enough to test the intervention, we will not collaborate with study physicians who conduct comprehensive medication reviews with medication management software or apply a PIM list as part of usual care for older cancer patients.

If no medication changes are discussed in the 2nd study visit, the study physician shall give the study participant the information that this could either mean that the medication review result was that no medication changes are necessary or that they were in the control group. As the exact wording is important in the communication with the patient to avoid accidental unblinding, the coordinating center will provide cards with the text to be communicated from the study physician to the patient in the two different scenarios (Medication changes suggested or not). The study physician shall read the text of the respective card to the patient.

Medication changes to be implemented after the 2nd visit should be documented by the study physician in a standardized form and communicated to the study participants’ general practitioners in the discharge letter. The standardized form should be mailed to the coordinating center.

#### Prescription monitoring

To check adherence of the study physicians regarding the implementation of the medication changes suggested by the FORTA list, a pharmacist in the coordinating center will conduct a second medication review with the FORTA list based on the information from the standardized form documenting the medication changes to be implemented after 2nd visit. Non-adherence of the study physician is defined by a FORTA score at rehabilitation clinic discharge worse by more than 2 points than the FORTA score of optimal medication as assessed by the coordination center in the first medication review. If non-adherence of a single study physician is much higher than that of most other study physicians, he/she will be excluded from further patient recruitment to the study.

It is theoretically possible that learning effects from using the advisory letters about medication changes in the intervention group get translated to the control group (so-called cross-contamination). Thus, all study physicians will be told that it is important that they do not change routine medical care during the study. As a measure to prohibit changes of routine care in the control group, the same prescription monitoring described above for the intervention group will also be applied to the patients of the control group. The average change in FORTA score from the first to the second visit for the first 10 control group participants for each study physician will be used as a baseline. If improvement in the FORTA score increases in control group participants during the study for certain physicians, they will be notified about this and asked to go back to their routine before starting the study. If this is not being done by the study physicians (or if it is not possible for them), they will be excluded from further patient recruitment to the study.

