### Endpoints

The primary endpoint of the study is the change of the European Organisation for Research and Treatment of Cancer’s Quality of Life Questionnaire’s Core 30 items (EORTC’s QLQ-C30 [10]) global health status (GHS)/QoL score. The GHS/QoL score can change in the time between filling of the baseline questionnaire (which takes place in the first 1–2 weeks of the rehabilitation clinic stay) and filling of the 8-month follow-up questionnaire (which takes place in study month 8–9). The GHS/QoL score is based on the following two questions: “How would you rate your overall health during the past week?” and “How would you rate your overall QoL during the past week?”, both of which have a scale from 1 (“very poor”) to 7 (“excellent”). According to the EORTC-QLQ-C30 manual, the two numbers are being summed up, the sum is being divided by two and subsequently standardized to a scale from 0 to 100 points.

The following Table 1 lists all endpoints that will be examined in the OPTIMAL study and the time-points of their assessment. Secondary endpoints will be the change of medication quality (total FORTA score and its sub-scores [7]) from rehabilitation clinic admission to discharge in week 3, other time-points of assessments of the GHS/QoL score (at 4- and 12-month follow-ups, which take place in study months 4–5 and 12–13, respectively), the other domains of the EORTC-QLQ-C30 including physical and cognitive functioning as well as symptom scores that often reflect adverse drug reactions (nausea, constipation diarrhea), dizziness, fatigue, frailty, falls, hospitalizations, as well as overall, non-cancer, and cancer-specific survival [10–12].

**Table 1 Tab1:** Outcomes and their Operationalization

Outcomes	Ascertainment/Operationalization	Time of assessment				
		Week 3	Month 4–5	Month 8–9	Month 12–13	Year 1–10
Total medication quality	Total FORTA score	x		x		
Medication underuse	FORTA medication underuse sub-score	x		x		
Medication overuse	FORTA medication overuse sub-score	x		x		
PIM use	FORTA PIM use sub-score	x		x		
Global health status	EORTC-QLQ-C30 questions: 29 + 30		x	x (primary)	x	
Physical functioning	EORTC-QLQ-C30 questions: 1–5		x	x	x	
Role functioning	EORTC-QLQ-C30 questions: 6,7		x	x	x	
Emotional functioning	EORTC-QLQ-C30 questions: 21–24		x	x	x	
Cognitive functioning	EORTC-QLQ-C30 questions: 20,25		x	x	x	
Social functioning	EORTC-QLQ-C30 questions: 26,27		x	x	x	
Dyspnoea	EORTC-QLQ-C30 question: 8		x	x	x	

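### As worded, the week-3 FORTA score comes from a form of planned changes but is treated as the score of the discharge medication; its effect on the arm comparison is unknown in size and direction

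*Protocol article*

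**What the plan says.** All references are to the protocol article.

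- **Endpoint.** *Endpoints* lists as a secondary endpoint "the change of medication quality (total FORTA score and its sub-scores [7]) from rehabilitation clinic admission to discharge in week 3". Table 1 schedules the FORTA outcomes at week 3 and month 8–9 only.
- **Baseline list.** The exclusion criteria in *Study population* show which information the first review needs: "medical diagnoses and drugs used at the start of rehabilitation". It is mailed to the coordinating center towards the end of week 1.
- **Form.** Under *2nd study visit*: "Medication changes to be implemented after the 2nd visit should be documented by the study physician in a standardized form". The abstract places implementation later still: the letter goes to the physician, "who shall discuss medication changes with the patient at the discharge visit, as well as implement them afterwards".
- **Second review.** *Prescription monitoring* has the pharmacist repeat the FORTA review "based on the information from the standardized form documenting the medication changes to be implemented after 2nd visit".
- **How the result is labelled.** The same section continues: "Non-adherence of the study physician is defined by a FORTA score at rehabilitation clinic discharge worse by more than 2 points". The month-8 adherence section and the per-protocol definition in *Statistical methods* also treat it as the score of the discharge medication, although the month-8 section calls that regimen intended.
- **Usual care.** In the control group "medication reviews and changes are not prohibited as they are sometimes done as part of usual care". Nothing confines such changes to the 2nd visit.

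**The concern.** The endpoint's name and its data source do not match. A score for the discharge medication needs the whole regimen at discharge. What is described is the admission list plus the changes agreed at one visit and still to be carried out. Two things follow.

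First, a drug started, stopped or replaced between the week-1 list and the 2nd visit falls outside the wording of the form, so the pharmacist would score that patient as if nothing had happened. Second, a change agreed at the visit counts as made, whether or not it ever is.

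At stake are the week-3 medication-quality result and four rules or references built on the same score: physician non-adherence with possible exclusion from recruitment, the per-protocol set, the reference for month-8 adherence, and the monitoring of control-arm drift.

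**Working it through.** **Which review feeds week 3.** Three reviews are described: one on the admission medication, one on the change form, and one on drugs in use at 8 months. With FORTA outcomes scheduled only at week 3 and month 8–9, the second review is the only described source for week 3. No discharge medication list is described as reaching the coordinating center; the discharge letter goes to the general practitioner.

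**Plan's own figure.** None is given for this endpoint. The stated sample size (231 per group, 462 in total, 514 with drop-out) belongs to the primary quality-of-life endpoint. It reproduces (power 0.8015 at 231 per group; 462/0.9 = 513.3, rounded up to 514) and has no bearing here.

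**Illustration.** The documents give no FORTA mean or rate of in-stay changes, so every input is an assumption:
- S = 4, the mean admission score;
- q = 15%, the share resolved by usual care before the 2nd visit, the same in both arms;
- a = 50%, the share of the remainder resolved through the letter, with no visit-2 changes in controls.

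True improvement:
- intervention S[q + (1−q)a] = 4 × (0.15 + 0.425) = 2.30;
- control Sq = 4 × 0.15 = 0.60;
- difference 1.70.

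| What the form captures | Intervention | Control | Difference |
|---|---|---|---|
| True | 2.30 | 0.60 | 1.70 |
| A. Early changes omitted in both arms | 1.70 | 0 | 1.70 |
| B. Letter prompts entry of problems already solved | 2.30 | 0 | 2.30 |
| C. A quarter of letter-driven changes made before the visit and left off | 1.275 | 0 | 1.275 |

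- **A** is the form read literally: S(1−q)a = 4 × 0.85 × 0.5 = 1.70 against 0. Each arm's change is understated by Sq = 0.60 (0.2 to 0.8 for q = 5% to 20%), but the difference is correct.
- **B** overstates the difference by Sq = 0.60. It is possible because the intervention letter is written from the admission list and can name a problem since resolved, while the control letter names none.
- **C** is possible because the letter arrives in week 2, before the visit: 1.70 × 0.75 = 1.275, an understatement of 0.425. For an early share of 10% to 50% the understatement is 0.17 to 0.85.

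If in-stay changes add FORTA problems instead of removing them, the within-arm error reverses sign.

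**The dependent rules.**
- *Physician adherence and per-protocol set.* A potentially inappropriate drug scores 2 points and an over- or underuse 1. One of each, both resolved before the visit and left off the form, keeps 2 + 1 = 3 points on the score. That exceeds the 2-point margin, so a physician who complied is classed as non-adherent and the intervention patient leaves the per-protocol set.
- *Month-8 reference.* A planned change never made can look like later non-adherence. An early fix left off makes the discharge score too poor and can hide a later deterioration.
- *Contamination check.* Each physician's controls are compared with that physician's own first 10. A physician who begins applying FORTA lessons to controls before the 2nd visit leaves no trace on the form.

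**The case against.** The form is not shown, and the article condenses a fuller protocol. A FORTA review needs a complete regimen, so the form may carry a current medication list or be read with an updated one. The text does not say that the form holds nothing else, and references to change between the first and second visit would fit an updated list. This stands as a limit: the omission of early changes follows from the wording of two sections, not from sight of the form. If a full list is collected, a sentence saying so settles that part.

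A reader might infer that the flaw favours the intervention, by as much as row B suggests (0.60/1.70 = 35%). The documents do not support this. It requires the form to be read literally for controls and loosely for the intervention arm, and no field for changes already made is described. Read the same way in both arms, the difference is 1.70 true and 1.70 recorded. Early action on the letter pushes the other way.

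The point about intentions is also limited. The 2nd visit is the discharge visit, a discharge letter is likewise a plan, and actual use is measured at 8 months.

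The reach has limits too. Per-protocol exclusions apply only to the intervention arm and serve a sensitivity analysis. In the contamination check a constant omission cancels within each physician; only new early drift escapes.

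**Conclusion.** The mismatch between label and source is real. Following the text as written mis-scores any patient whose drugs changed between the week-1 list and the 2nd visit, and scores an intended regimen as the discharge medication. Each arm's change can be wrong, physicians can be misclassified, and early control-arm drift can go unseen.

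The effect on the between-arm difference is unknown in size and direction: zero with equal omission, positive under B, negative under C. The numbers above show only the mechanism and rest on assumed S, q, a and early share.

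It would go too far to say that the endpoint cannot show any difference in medication quality at discharge. The endpoint is secondary, the plan declares it exploratory, and the primary quality-of-life analysis does not use it.

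**What to change.** In both arms, score the week-3 FORTA endpoint and every rule that uses it from the complete medication list at discharge. The source can be a pseudonymized copy of the medication list in the discharge letter, or a full-list field on the form that clinics already mail. Keep the change form as a process record of what was agreed at the 2nd visit. Label the endpoint as the FORTA score of the medication prescribed at discharge, since even a complete list records prescribing and not use; the month-8 review covers use.

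The cost is one existing page per patient to copy and pseudonymize, or one added field on the form. No new visit is needed, and the primary analysis and sample size are unchanged.
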